### Treatment protocols

The intervention protocols for both groups will be outlined in a detailed treatment manual, supplemented by a digital clinical notes template. The template will detail the intervention in accordance with the study protocol for all sessions. Intervention programs will be matched for time exposure to the physiotherapist, with both groups having six sessions over a 12-week period, at 0, 1, 2, 3, 6- and 12-weeks post randomisation. For both groups the first session will be 1 h in duration with follow-up sessions 30 min.

#### SHOCKWAVE intervention

Intervention in the SHOCKWAVE group will follow the approach of Cacchio et al. [2] consisting of four sessions of ESWT at weekly intervals in accordance with a standardised protocol. There will be no ESWT in the final two sessions, which will be used to review relevant information sheets and plan for return to normal activities.

Although the trial on PHT by Cacchio et al. [2] used only radial shockwave, both radial (EMS Swiss Dolorclast, Milano, Italy) and semi-focused shockwave (Dornier, Germany) will be used as research has found no difference in outcomes between the two different devices in tendinopathy [56]. Shockwave dosage will be 2000 shocks per session at the highest tolerable intensity which appears to be a safe and effective dose [56].

#### PHYSIOTHERAPY intervention

Intervention in the PHYSIOTHERAPY group will relate to known or hypothesised mechanisms underpinning PHT and be informed by treatment shown to be effective in other lower limb tendinopathies [57, 58]. A key component of the program will be a multi-stage, progressive, individualised, strengthening/rehabilitation program, with consideration given to sporting and occupational demands. Graded reintroduction of compressive forces in loading programs is recommended for PHT [3, 59] and other lower limb tendinopathies [60–63] and will be incorporated in the PHYSIOTHERAPY intervention algorithms.

Pain monitoring, both during and latent to loading, is a key component of the intervention. Use of a pain ‘ceiling’ during rehabilitation is thought to provide a safe guideline for exercise loads and avoids the need for a prolonged period of rest in which only pain free activity is allowed. Pain levels of up to 4/10 on a NPRS were permitted, with treating physiotherapist discretion in the presence of higher baseline OMPSQ-SF scores or in the first two repetitions of isometric exercise providing symptoms reduce over this time. A significant increase in symptoms lasting over 24 h after activity is thought to indicate excessive loading of the tendon [3, 14, 64, 65] although the biological mechanism of this response is unknown.

Stage 1 of the PHYSIOTHERAPY intervention will comprise isometric hamstring exercise aiming to safely commence strengthening the hamstring complex, increase motor drive [66] and reduce pain levels. [66]. Stage 2 will incorporate isotonic strengthening exercises of the hamstring musculature. Stage 3 will add kinetic chain exercises including strengthening of agonist muscles, and stage 4 will reintroduce compressive load by increasing the hip flexion angle of hamstring strengthening exercises. The final 5^th^ stage will involve high speed (energy storage and release) exercises included if required for sporting/occupational demands, e.g. field/court sports. Exercises options that are specific to sporting/occupational demands will be chosen where possible. Retraining of lower limb kinetic chain movements (e.g. lunge, squat, running) and lumbopelvic control rehabilitation will be incorporated if indicated by the assessment of the treating physiotherapist in line with recommendations for other lower limb tendinopathies [14, 64]. Progression to later stages of the program will be criteria driven, with demonstrated load tolerance (stable symptoms during, and following, rehabilitation and activity), and strength (compared to the unaffected side) used. Return to sport advice will be provided. The treatment protocols have been developed by the research team including a clinical/research expert in this area (JC) and published elsewhere (manuscript in preparation).

#### Participant education and other co-interventions

Standardised pre-prepared information sheets will be provided to both the SHOCKWAVE and PHYSIOTHERAPY groups. The information sheets will include topics explaining diagnosis, treatment options, expected recovery timeframes, monitoring pain, the role of compression (including sitting) in tendinopathy, and high and low tendon loading activities. Information sheet content will be developed based on known or hypothesised mechanisms underlying physiotherapy treatment of this condition. Management of medication will not be a focus of treatment and will be consistent between groups. Therefore medication use will be measured at baseline only and will not be followed up over time, however physiotherapists will be able to refer participants to a pharmacist or their general practitioner during the treatment program if they determine that medication review is warranted.

#### Participating physiotherapists and treatment fidelity

Physiotherapists from private practices in Victoria will provide treatment for both groups. To be eligible, the physiotherapists will need to have at least 2 years of clinical experience. Physiotherapists will then participate in a small group, 4-h training session provided by the lead researcher (AR). The program will include review of previously provided material, and simulation of explanations and treatments to be used in the trial.

Treating physiotherapists will be provided with a treatment manual detailing treatment algorithms, protocols and participant information sheets. Treatment methods will be clearly defined and standardised via a detailed session-by-session electronic clinical notes template containing a series of decision-making algorithms. The algorithms and clinical notes will ensure that essential elements of the treatment program are consistently applied by all physiotherapists across all participants, while still allowing some opportunity for the treatment to be tailored to individual participant presentation. The template will require treating physiotherapists to provide physical assessment findings, justification and rationale for clinical decision making, detail of treatment provision/prescription and response to treatment. Physiotherapists will be required to complete electronic clinical notes for each session which detail assessment findings, treatment provided, clinical decision-making justification and any adverse events from shockwave treatment or the exercise program.

A quarterly face-to-face meeting will be undertaken for 60 min involving all treating physiotherapists for the duration of the trial to review de-identified cases in the context of the treatment protocol. Evaluation of treatment fidelity and adherence by the physiotherapists for specific rehabilitation techniques will be achieved by checking the physiotherapist’s clinical notes for each participant after the second and fourth sessions of the program.

### Outcome assessment

Outcomes will be assessed through self-administered electronic questionnaires on QuestionPro, except for hamstring strength that will be assessed by a blinded assessor. Weblinks to the questionnaires will be emailed to participants at the appropriate time points (Table 2). Outcome measures adhere to the consensus guidelines for tendinopathy health domains, [67] and patient reporting characteristics (for baseline data) [68]. Feasibility for this trial will be measured with recruitment rate, participant retention, and completion of outcome measures.

**Table 2 Tab2:** Outcome measures

Outcome measure	Measurement point (weeks)
**Primary outcome measures**	
1. Global rating of change scale (7-point Likert scale)	4, 12, 26, 52
2. VISA-H (8-item questionnaire)	0, 4, 12, 26, 52
**Secondary outcome measures**	
1. Sitting tolerance (5-point scale)	0, 4, 12, 26, 52
2. Modified Physical Activity Level Scale (6-point scale)	0, 4, 12, 26, 52
3. Eccentric hamstring strength (nM)	0, 12
4. Modified Tampa scale for kinesiophobia (TSK-11) (11-item questionnaire)	0, 4, 12, 26, 52
5. Örebro Musculoskeletal Pain Screening Questionnaire Short Form (ÖMPSQ-SF)	0, 4, 12, 26, 52
6. Pain Catastrophizing Scale (PCS)	0, 4, 12, 26, 52
7. Numerical Pain Rating Scale (average and most severe pain over previous week)	0, 4, 12, 26, 52
8. Participant and physiotherapist rating of adherence (11-point Likert scale)	4, 12, 26, 52
9. Satisfaction with treatment (5-point Likert scale)	4, 12, 26, 52
10. Satisfaction with the results of treatment (5-point Likert scale)	4, 12, 26, 52
11. EuroQoL-5D	0, 4, 12, 26, 52

#### Primary outcome measures

Global rating of change will be measured using a 7-point Likert scale, with participants rating their overall change from baseline [69, 70]. Various versions of this scale are considered to be reliable, responsive and valid [70, 71].

Pain, function and sporting activity will be measured with the VISA-H (Victorian Institute of Sport – Hamstring) questionnaire [72]. The VISA-H has been shown to be valid, reliable and responsive for measuring pain, function and sporting activity in people with PHT [72].

#### Secondary outcome measures

Pain with sitting is a common feature of PHT [3] and this will be measured using a Patient Specific Functional Scale (PSFS) [73]. The PSFS is validated and reliable for measuring change with specific functional activities in musculoskeletal conditions [74–78].

Functional restrictions due to the condition will be measured with the modified Physical Activity Level Scale [58, 79] which is validated for measuring physical activity [80]. Eccentric hamstring strength will be measured with the NordBoard (Vald Performance, Albion Queensland) device. Reduced strength has been identified as a risk factor for development of tendinopathy by an expert panel, [81] and many physiotherapy programs incorporate strength exercises. This is a reliable method of testing eccentric knee flexor forces during the Nordic hamstring exercise without provoking symptoms [82].

Three questionnaires will be used to measure psychosocial outcomes. The Orebro Musculoskeletal Pain Screening Questionnaire Short Form (OMPSQ-SF) will be used as an overall measure of psychosocial risk factors. This OMPSQ-SF has been validated for persistent and musculoskeletal conditions, [83] and contains subsections for measuring fear avoidance beliefs, recovery expectations, depression and anxiety. Kinesiophobia will be measured with the Modified Tampa scale (TSK-11) [84]. Kinesiophobia has previously been shown to be associated with some tendinopathies such as rotator cuff [85] but not others, such as lateral elbow tendinopathy [86]. Kinesiophobia appears to be a risk factor for poor outcome in Achilles tendinopathy [87]. The Pain Catastrophizing Scale (PCS) [88] will be used to measure catastrophising. Catastrophising has been shown to be associated with pain and disability in other lower limb tendinopathies [89].

Severity of symptoms will be assessed with the Numerical Pain Rating Scale (NPRS), with participants asked to report their average and worst pain over the preceding week. The NPRS is valid and reliable for musculoskeletal conditions [90].

Participant adherence will be measured using the number of sessions attended, and with participant and physiotherapist report of adherence to treatment [91].

Participants will rate their satisfaction with treatment and their satisfaction with the results of treatment on separate 5-point Likert scales [92–94]. These scales have good reliability, validity and responsiveness [95, 96].

Health-related quality of life will be measured with the EuroQoL-5D, [97] which is valid and responsive in chronic musculoskeletal pain [98].

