**Methods:**

The study is an assessor-blinded, pilot randomised controlled trial (RCT). One hundred participants with PHT will be recruited from the local community and sporting clubs. Participants will be randomised to receive six sessions of either individualised physiotherapy or ESWT, with both groups also receiving standardised education and advice.

Primary outcomes will be global rating of change on a 7-point Likert scale, and the Victorian Institute of Sport—Hamstring (VISA-H) scale, measured at 0, 4, 12, 26 and 52 weeks. Secondary outcomes will include sitting tolerance, the modified Physical Activity Level Scale, eccentric hamstring strength, modified Tampa scale for kinesiophobia, the Örebro Musculoskeletal Pain Screening Questionnaire Short Form (ÖMPSQ-SF), Numerical Pain Rating Scale (NPRS) for average and worst pain, participant adherence, the Pain Catastrophizing scale, satisfaction scores, and quality of life. Data will be analysed on an intention to treat basis, with between-group effects estimated using linear mixed models for continuous data and Mann Whitney U tests for ordinal data.

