#### Treatment effects

Following trial completion, data from all follow-up points (4, 12, 26- and 52-weeks following randomisation) will be analysed, focussing on between-group treatment effects (with 95% confidence intervals). SPSS will be used to conduct analyses. Alpha will be set at 0.05 using a two-tailed hypothesis.

Intention to treat principles will be used for all analyses; with participants analysed based on their original allocation regardless of their adherence with treatment or number of sessions attended [101]. Missing data will be managed by maximum likelihood estimation within linear mixed models [102].

Continuous data will be analysed using linear mixed models, adjusting for baseline values and the stratification variable of age (with the group x time interaction estimating the between-group treatment effect). Ordinal data will be analysed using the Mann Whitney U test at each timepoint. It is acknowledged that this will increase the Type 1 error rate however this only applies to some secondary outcomes and is offset in part by the lower power associated with non-parametric tests.

A responder analysis will also be undertaken to determine the proportion of participants who achieved clinically important changes on outcome measures. For these purposes, the minimum clinically important difference (MCID) for individuals will be defined as 12 points on the VISA-H questionnaire [72], and at least ‘much improved’ on the global rating of change scale [103, 104]. The MCID value for the VISA-H was used as it is similar to MCID values on other VISA scales [105–108]. For responder analyses, the risk ratio, risk difference and number needed to treat will be calculated along with 95% confidence intervals [109]. Statistical significance for the responder analyses will be evaluated using Chi square analysis.

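### Table 2 and the outcome text describe the sitting outcome differently, which leaves its instrument, and so its data type and test, undetermined

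*Protocol article*

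**What the plan says.** The protocol article describes the sitting outcome in three places.

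- **Table 2, secondary outcomes:** "1. Sitting tolerance (5-point scale"), measured at weeks 0, 4, 12, 26 and 52.
- **Abstract, Methods:** "Secondary outcomes will include sitting tolerance, the modified Physical Activity Level Scale, eccentric hamstring strength", with no instrument named for sitting.
- **Text, Secondary outcome measures:** of pain with sitting, the article says "this will be measured using a Patient Specific Functional Scale (PSFS"). The next sentence gives the measurement properties: "The PSFS is validated and reliable for measuring change with specific functional activities in musculoskeletal conditions".

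The Treatment effects section then sets the analysis by type of data. For one type, "Continuous data will be analysed using linear mixed models, adjusting for baseline values and the stratification variable of age", with missing data handled by maximum likelihood within those models. For the other, "Ordinal data will be analysed using the Mann Whitney U test at each timepoint", with no adjustment mentioned. The sitting outcome is not assigned to either type.

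**The concern.** Tolerance of sitting and pain with sitting are different labels for what is measured. A 5-point scale and the Patient Specific Functional Scale (PSFS) are named as if they were different instruments. Table 2 and the abstract do not mention the PSFS, and the text does not mention a 5-point sitting scale. A reader cannot tell which question participants answer.

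Two things follow. First, the validity and reliability statement belongs to the PSFS. If participants complete the 5-point scale in Table 2, nothing in the article shows that this evidence covers it. Second, the analysis rule depends on data type, and data type depends on the instrument. One branch is a single longitudinal model that adjusts for baseline and age stratum and uses all observed visits. The other is a separate unadjusted rank test at each of four follow-ups.

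Sitting is a leading symptom of this condition and one of the four eligibility tests. The pilot is also meant to supply estimates for a definitive trial, which needs to know what the scale was.

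**Working it through.** **1. The descriptions side by side**

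| Place | Construct | Instrument | Response scale |
|---|---|---|---|
| Abstract | Sitting tolerance | Not named | Not given |
| Table 2 | Sitting tolerance | Not named | 5-point |
| Text | Pain with sitting | PSFS | Not given |

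The Table 2 row is intact, so this is not damage from text extraction. Other Table 2 rows, such as the modified Physical Activity Level Scale, TSK-11, PCS, NPRS and EuroQoL-5D, carry the same instrument name in the text.

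**2. What the analysis rule gives**

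- If the item is the 5-point scale, it would ordinarily count as ordinal. The rule then gives Mann-Whitney tests at weeks 4, 12, 26 and 52. At the stated two-sided alpha of 0.05, the chance of at least one false positive over four independent tests is 1 − 0.95^4 = 18.5%. Positive correlation between visits would lower this.
- If the item has a score treated as continuous, the rule gives one mixed model. Whether the PSFS is such a score cannot be read from the article, which gives no range for it.

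So the rule is clear and the input to it is missing.

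**3. The plan's own sample size figure**

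Inputs from the Sample size section: standardised difference 0.6, 80% power, 10% loss, total 100. Equal allocation is assumed.

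- Normal approximation: n = 2 × (1.96 + 0.84)² / 0.6² = 43.6, so 44 per arm. Then 44 / 0.9 = 48.9, so 49 per arm and 98 in total.
- t-test: 44.6, so 45 per arm. Then 45 / 0.9 = 50 per arm and 100 in total.

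The figure of 100 reproduces, and settling the sitting instrument does not change it.

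**4. Illustration of what the analysis choice is worth**

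Assumed for this outcome: 45 per arm analysed, a true effect of 0.6 SD, a normal underlying variable cut into five levels, and a correlation r between the week-0 and follow-up values. The article gives no r, so a range is shown. Power comes from simulation, apart from the t-test, which is calculated.

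| Analysis | r = 0.3 | r = 0.5 | r = 0.7 |
|---|---|---|---|
| Unadjusted t-test, continuous score | about 80% | about 80% | about 80% |
| Mann-Whitney, five levels | about 77% | about 75% | about 77% |
| Ordinal model adjusted for week 0, five levels | about 78% | about 83% | about 94% |
| Baseline-adjusted linear model, continuous score | about 84% | about 89% | about 98% |

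The true power of Mann-Whitney does not depend on r; repeat runs gave 74-77%, and the differences along that row are simulation noise. Within the 5-point scale, adjustment gains about 78 − 77 = 1, 83 − 75 = 8 and 94 − 77 = 17 points. The coarser scale and rank test alone cost about 80 − 77 = 3 to 80 − 74 = 6 points. The gain therefore comes mainly from using the baseline value, and it is small if that value predicts follow-up weakly.

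**The case against.** The strongest reply is that the two descriptions may be one item, incompletely described. The text speaks of a PSFS in a general way and presents it as a measure for particular activities; sitting is one. A PSFS-style sitting question with five response options would satisfy both Table 2 and the text. A journal article condenses the full protocol, and item wording is often left there. This stands as far as it goes: two separate instruments are not proved. But the article does not state this reading, and on it the item would be an adapted scale, so the text would still need to say so and to justify the validity claim for it.

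A reader might also infer that the plan prescribes two incompatible tests for one outcome. The document does not support that. It gives one general rule, never assigns this outcome to both branches, and does not state the PSFS score range that would make it continuous. The only response format on the page is 5-point.

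A reader might further infer that the test could be picked freely after seeing the data. That goes too far. Outcomes are collected on electronic questionnaires, so the form already issued fixes the response format, and the Blinding section says that analysis uses data without identifying group labels. The remaining discretion is narrow.

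Finally, comparing the adjusted continuous analysis with Mann-Whitney would suggest a gap of roughly 8-22 points of power. Most of that reflects baseline adjustment at assumed correlations, not the mismatch in labels, and the 0.6 SD effect is the article's illustration for measures such as the VISA-H. The article also says that the trial is not fully powered.

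**Conclusion.** The inconsistency is real. Table 2 and the abstract name sitting tolerance, the text names pain with sitting on a PSFS, and nothing connects them. The instrument is therefore undetermined, and with it the data type and the test.

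The severity is minor. One of 11 secondary outcomes is affected; the primary outcomes, the sample size of 100 and the feasibility thresholds are not. What lifts the point above a labelling correction is that the week-0 value is already collected and an unadjusted rank test would not use it. The size of that benefit, from about 74-77% power to about 78-94%, holds only under the assumed effect, numbers per arm and correlations of 0.3 to 0.7. It should not be read as an estimate for this trial.

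**What to change.** 1. Use one construct, one instrument and one response scale for the sitting outcome in Table 2, the abstract and the text, matching the questionnaire actually issued. If it is an adapted PSFS item with five options, say so.
2. Keep the PSFS validity and reliability sentence only if that evidence applies to the item used.
3. State the analysis of this outcome before unblinding. If the item is the 5-point scale, replace the unadjusted Mann-Whitney test at each timepoint with an ordinal model (for example, proportional odds) adjusted for the week-0 value and the age stratum. If the item is scored as continuous, use the mixed model already planned.

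The cost is a correction to the text and table and a short addition to the analysis section. No new data are needed, because sitting is already recorded at week 0.

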### Adverse events

Adverse events occurring during the treatment period will be recorded by the physiotherapist in the standardised clinical notes of each participant. Any serious adverse events will be immediately reported to the lead researcher, who will investigate and organise medical care (if required) and report to the ethics committee. The lead researcher will review the clinical notes and questionnaires after 4 weeks of treatment to screen for any unreported adverse effects of treatment. Participants will be provided opportunity on follow-up questionnaires to report any unpleasant, adverse, or harmful effects they ascribe to the treatment.

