### Blinding

It is not feasible to blind participants or treating physiotherapists due to the nature of the interventions. However, treating practitioners and researchers will inform participants that both treatment approaches have a realistic chance of providing success and that neither has been shown to be superior in previous trials. Physiotherapists will be advised to treat both groups of participants with the same level of expectation and enthusiasm. Strength outcomes will be measured by a blinded assessor. Data analysis will be performed using data without identifying group labels, to ensure blinded analysis.

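### Two sections disagree on which adverse events physiotherapists record, and after week 12 the only stated route for non-serious events is limited to effects that unblinded participants attribute to treatment

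*Protocol article*

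**What the plan says.** The article describes four routes for adverse events, three of them in the Adverse events section alone.

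- **Physiotherapist's notes.** The Adverse events section says "Adverse events occurring during the treatment period will be recorded by the physiotherapist in the standardised clinical notes of each participant". This sets no condition on cause. The section Participating physiotherapists and treatment fidelity, listing what the electronic notes for each session must contain, has "any adverse events from shockwave treatment or the exercise program".
- **Serious events.** "Any serious adverse events will be immediately reported to the lead researcher". There is no condition on cause and no stated end date.
- **Central check.** After 4 weeks of treatment the lead researcher reviews notes and questionnaires to "screen for any unreported adverse effects of treatment".
- **Participant questionnaires.** "Participants will be provided opportunity on follow-up questionnaires to report any unpleasant, adverse, or harmful effects they ascribe to the treatment".

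The Blinding section states "It is not feasible to blind participants or treating physiotherapists due to the nature of the interventions". Under Treatment protocols, treatment means "both groups having six sessions over a 12-week period". Under Treatment effects, "data from all follow-up points (4, 12, 26- and 52-weeks following randomisation) will be analysed".

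**The concern.** Two rules are given for one record. A template built on the fidelity section would leave out events that the Adverse events section requires, for example a new symptom that the physiotherapist thinks unrelated.

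The participant questionnaire asks for a causal judgement before anything is written down, and the person judging knows the allocation. Once physiotherapist recording stops at the end of treatment, no other route for non-serious events is stated.

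The protocol itself makes unequal attribution plausible. Discomfort after a shockwave session has an obvious cause. A flare during a loading programme that tolerates some pain (up to 4/10 on the NPRS) can be read as expected soreness or as the tendinopathy itself. In addition, the four shockwave sessions fall at weeks 0 to 3, so the single central check comes after the whole shockwave course, whereas the exercise programme progresses through its stages up to week 12 with no later check described.

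At stake is whether harms reported by arm reflect how often events occurred or what people believed caused them. A definitive trial built on this pilot could inherit the same instruments.

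**Working it through.** The article states no adverse-event rate and no figure for harms, so there is nothing to reproduce. The check is a comparison of the routes, followed by an illustration.

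**Step 1: the routes side by side**

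| Route | Period | Limited to effects of treatment? | Who judges |
|---|---|---|---|
| Session notes, Adverse events section | Treatment period (12 weeks) | No | Not applicable |
| Session notes, fidelity section | Each session | Yes (events must come from the shockwave or exercise) | Physiotherapist, unblinded |
| Serious events | No end stated | No | Not applicable |
| Central check | Once, after 4 weeks of treatment | Yes | Lead researcher |
| Participant questionnaires | Follow-up points | Yes | Participant, unblinded |

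The first two rows describe the same document with different scope. That is the contradiction. The questionnaire sentence alone contradicts nothing; it adds a further, narrower route.

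The lead researcher's check is not a blinded one. The article identifies the lead and primary researcher as the same person, and under Randomisation and allocation the primary researcher is told each participant's allocation.

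**Step 2: the period with one route**

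Follow-up ends at week 52 and treatment at week 12: 52 - 12 = 40 weeks in which the questionnaire is the only stated route for non-serious events.

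**Step 3: what a filter does to the comparison**

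For events that reach the record only through an attribution filter:

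recorded risk = true risk x probability of attribution.

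If the true risk is the same in both arms, the recorded risk ratio equals the ratio of the two attribution probabilities. All inputs below are assumed.

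| True risk, both arms | Attribution, arm A / arm B | Recorded, A / B | False difference | False ratio |
|---|---|---|---|---|
| 30% | 0.90 / 0.70 | 27% / 21% | 6 points | 1.29 |
| 30% | 0.90 / 0.50 | 27% / 15% | 12 points | 1.80 |
| 10% | 0.80 / 0.60 | 8% / 6% | 2 points | 1.33 |
| 20% | 0.80 / 0.40 | 16% / 8% | 8 points | 2.00 |
| 30% | 0.70 / 0.70 | 21% / 21% | 0 points | 1.00 |

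For example, 0.30 x 0.90 = 0.27, 0.30 x 0.50 = 0.15, and 0.27 - 0.15 = 0.12.

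The last row shows both halves of the point. Equal attribution leaves the ratio intact, but 1 - 0.70 = 30% of events are still lost in each arm. A false difference appears only if attribution differs by arm.

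**The case against.** A reader might infer that no adverse event is recorded unless someone blames the treatment, and that the harm comparison is therefore biased. The documents do not support that.

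- The opening sentence of the Adverse events section and the sentence on serious events carry no condition on cause. The fidelity section's phrase could be a loose summary of the same notes rather than an override. This stands: whether non-serious events in the treatment period are filtered depends on which sentence the template follows, and the article leaves that open.
- Worsening symptoms are visible elsewhere. Average and worst pain over the previous week and VISA-H are collected in everyone at 0, 4, 12, 26 and 52 weeks, global change is rated at each follow-up, and session notes record the response to treatment. None of these depends on attribution. This stands for persistent worsening. The pain ratings cover one week per time point, so they miss transient flares, and none of these measures identifies events outside the hamstring.
- Harms are not among the outcomes in Table 2, and Treatment effects describes no comparison of them. This stands: the exposure is in any by-arm report of harms, not in a named analysis.
- Unequal attribution is assumed, and its direction is uncertain. The questionnaire also invites unpleasant effects, a broad prompt that could pick up exercise soreness. This stands, and the illustration overstates the effect wherever the unconditional routes operate.
- The template and questionnaires are separate documents, and the article may paraphrase them. They may prove to be worded more widely, but the article as written gives two scopes.

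**Conclusion.** The point holds in limited form. The two sections disagree on the scope of the physiotherapist's record and must be reconciled. For the 40 weeks after treatment, non-serious events reach the adverse-event record, by any stated route, only if an unblinded participant attributes them to treatment. Those not attributed are lost as adverse events, although some may show indirectly in the pain and function scores.

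Distortion between arms is a possibility, not a finding. It requires attribution to differ by arm, which the open design and the nature of the two treatments make plausible but the article does not show. The 6-12 point figure rests wholly on an assumed 30% risk and assumed attribution probabilities, and treats attribution as the only filter. It shows how the mechanism works and is not an estimate for this trial. The matter is worth correcting because events not recorded cannot be restored in analysis and the correction is cheap. It does not bear on the primary outcomes.

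**What to change.** Give the fidelity section and the Adverse events section the same scope. In the session notes and all remaining follow-up questionnaires, ask in identical words in both arms for any new or worsened symptom or health event since the last contact, whatever its presumed cause. Record relation to treatment in a separate field completed afterwards. Report all events by arm first, then those judged related. Report data collected under the existing wording separately from data collected under the new wording.

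The cost is a change to the electronic template and questionnaire, one added field and more trivial events to process. There will also be two wording versions: final recruitment was expected in early 2023 and this protocol version is dated 7 March 2023, so much of the treatment contact will probably have taken place under the existing wording. Within this trial the gain would fall mainly on the later questionnaires; the larger gain is to the instruments that a definitive trial would take over.
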